## Abstract

**Background:**

Maternal prenatal depressive or anxiety symptoms are associated with adverse maternal and infant health outcomes. With prevalence rates of maternal prenatal depression and anxiety ranging between 10 and 20%, attempts to identify effective interventions to reduce symptoms are priority. There are indications that probiotics can reduce symptoms of maternal depression or anxiety. Probiotics ingested by the mother may thus offer a promising and accessible intervention to complement existing treatments.

**Methods:**

The Probiotics in Pregnancy (PIP) pilot trial is a double-blind, placebo-controlled, randomized pilot trial. While one group orally consumes a probiotic mixture (Ecologic® Barrier; 2,5 × 109 colony forming units/g; 2 g; daily), the other group consumes a placebo, from between 26 and 30 weeks gestation until delivery. Subjects are randomly allocated (1:1) to the intervention or placebo group. Forty healthy pregnant women with symptoms of depression or anxiety and uncomplicated pregnancies at randomization will be included. The primary aim is to determine the feasibility and acceptability of a probiotic trial to reduce symptoms of maternal depression or anxiety in pregnancy. The secondary aim is to exploratorily compare the potential effect of probiotics, compared to placebo, on depressive and/or anxiety symptoms, maternal stress (i.e. reported/hair cortisol), maternal vaginal and intestinal microbiota, and by possibly affecting maternal mood and microbiota, maternal bonding to offspring, infant microbiota and infant crying.

**Discussion:**

Results of this pilot trial will help determine whether or not to proceed with a full trial after the pilot trial, and if so, whether revisions should be made to the study protocol and procedures before conducting a full randomized controlled trial. Additionally, they are expected to provide insights into whether changes in psychological, behavioral and biological parameters can be attributed to the probiotic intervention.

**Trial registration:**

Netherlands Trial Register, NTR6219. Registered on 28 February 2017.

**Electronic supplementary material:**

The online version of this article (10.1186/s13063-019-3389-1) contains supplementary material, which is available to authorized users.

## Background

Pregnancy can be an exhilarating time for expectant mothers. However, pregnancy can also be accompanied by sadness and worry, as 10–20% of pregnant mothers report anxiety and depressive symptoms [1, 2]. Counseling and medical treatments are effective to reduce symptoms of maternal prenatal depression or anxiety. However, relatively few women engage in treatment [2, 3]. This can, in part, be explained by reluctance to use medication prenatally, therapies being inaccessible to women and/or long waiting lists for treatment [4, 5]. Hence, there is a need for safe, accessible and effective complementary interventions to treat maternal prenatal depression and anxiety. Probiotics may reduce symptoms of depression and anxiety in people with elevated levels of anxiety and/or depression [6]. In the current study, we will investigate the feasibility and acceptability of conducting a probiotic intervention from 26 to 30 weeks gestation until birth, for reducing maternal prenatal symptoms of depression or anxiety.

### Probiotics for maternal mood

Probiotics are live organisms that, consumed in adequate amounts, confer a health benefit to the host [7]. Probiotics, with their anti-inflammatory and neuro-regulatory properties, may improve gut microbiota composition and functioning, consequently improving mood [8–10]. Previous systematic reviews found that probiotics can indeed reduce depressive symptoms [11–13]. However, the recent high-quality systematic review by Ng et al. in 2018 [11] concluded that probiotics are only effective in non-pregnant people with pre-existing symptoms of anxiety or depression. In pregnant women, a recent randomized controlled trial (RCT) with a low risk of bias showed that a probiotic intervention during the perinatal period significantly reduced symptoms of maternal depression and anxiety postpartum, compared to mothers receiving a placebo [14, 15]. To date, no studies have investigated the potential effectiveness of probiotics during pregnancy to improve maternal mood.

RCTs are judged the “gold standard” to evaluate the therapeutic efficacy of psychological treatments [16, 17]. The success of a RCT in pregnant women largely depends on two factors: women’s willingness to participate in the study and compliance to the intervention during the trial [18, 19]. In order to increase chances of success of a potential future RCT, it is of value to first assess *feasibility* (i.e. whether the future trial can be done) and *acceptability* (i.e. participants’ adherence and satisfaction with the study) of the study protocol by employing a pilot trial [20, 21].

### Objectives

The main aim of this pilot trial is to evaluate the feasibility and acceptability of conducting a definitive RCT among pregnant women with symptoms of depression or anxiety. Feasibility is evaluated in terms of (A) recruitment and (B) retention, and acceptability is evaluated in terms of (C) compliance and (D) participants’ experiences of participating in the study. The primary objectives are to quantitatively and qualitatively assess (A) the proportion of pregnant women with depressive and/or anxiety symptoms accepting the invitation to participate in the pilot trial and the reasons why (quantitative and qualitative), (B) the proportion of women who complete the study (quantitative), (C) adherence rates to the intervention schedule (i.e. probiotic/placebo intake, questionnaires and biological sample collection) (quantitative) and (D) participants’ impressions and experiences during the pilot trial (quantitative). The secondary aim is to exploratorily compare the potential effect of probiotics, compared to placebo, on depressive and/or anxiety symptoms, maternal stress (i.e. reported and hair cortisol), maternal vaginal and intestinal microbiota, and by possibly affecting maternal mood and microbiota, maternal bonding to offspring, infant microbiota and infant crying. The purpose of collecting these secondary outcomes will be to ensure that the potential effects of probiotics on maternal mood, and the mechanisms underlying these potential effects, can be assessed appropriately in a future definitive RCT.

## Methods

### Trial design

This probiotic intervention project in mothers and their infants is a double-blind, randomized pilot trial (RCT) (probiotic intervention versus placebo). Forty healthy pregnant women (≥ 18 years of age) with at least mild depressive symptoms and/or anxiety in the late second/third trimester of an uncomplicated pregnancy (≥ 26 and ≤ 30 weeks gestation) will be enrolled in this study (see Fig. 1). Participants will orally consume a probiotic multispecies mixture (Ecologic® Barrier; 2,5 × 10^9^ colony forming units (CFU)/g per dosage; daily dosage 2 g) once daily, or a placebo, for 8–14 weeks consecutively (depending on the time of delivery). Detailed information on the intervention components is provided under “Intervention procedures”. For more information on the protocol items, please refer to the Standard Protocol Items: Recommendations for Interventional Trials (SPIRIT) checklist (Additional file 1).

**Fig. 1 Fig1:**
[figure not shown]
Standard Protocol Items: Recommendations for Interventional Trials (SPIRIT) figure displaying the pilot trial design and the outcome measurements. After screening for eligibility (t-1), women sign the informed consent form and complete the baseline questionnaire (t0). Participants are then randomized in the probiotic or placebo arm and receive either the probiotic food supplement or placebo. After randomization, filling in the baseline questionnaire and collecting maternal vaginal and stool samples, women start using either the probiotic food supplement or placebo. Measurements take place at 26–30 weeks of pregnancy (baseline(t0); 34–38 weeks of pregnancy (t1); 7 days after birth (t3), and 1 month after birth (t4)).

### Study setting and recruitment

#### Recruitment procedures

Recruitment methods in the pilot will mimic those of a full RCT. Recruitment will take place in collaboration with two ultrasound centers (VCN/CVN and Fara), a lactation consultant practice (Fijn Voeden), two mental health centers (Praktijk Moeder and Mental health center [name]) and an academic hospital (Radboud university medical center) in the Netherlands. These different centers and clinics were chosen because they serve ethnically and socioeconomically diverse, low-class and high-class populations.

#### Screening process and participant flow

Potentially eligible women are identified through two mechanisms: (1) local research advertising and (2) identification in the research database. Women visiting echo center Fara (around 200 per month) will receive an e-mail invitation for an online questionnaire after their 20-week ultrasound scan. The e-mail will be sent by a Fara organizational committee member. At the second echo center (VCN/CVN), women who visit the centers for their 20-week echo will receive a flyer and can sign up to receive the online questionnaire by providing their e-mail addresses. Research assistants at the Radboud University will collect these e-mail addresses and send the women an e-mail invitation for the online questionnaire. Flyers with a link to the online questionnaire are placed in the waiting room at the academic hospital, the lactation consultant practice and the mental health centers. In this way, women can directly access the online questionnaire. The questionnaire forms part of another study investigating the psychosocial needs of women during pregnancy, which is approved by the Ethics Committee of the Faculty of Social Sciences ECSW (registration number: ECSW2016–1710-42, registration date 19 December 2017). Women voluntarily give informed consent before filling in the online questionnaire. The online questionnaire consists of the Edinburgh Postnatal Depression Scale (EPDS), State-trait Anxiety Inventory, State (STAI-S), questions on demographic variables (e.g. general health, maternal lifestyle, sociodemographic and economic factors) and open questions on psychosocial needs, barriers and facilitators to mental healthcare use. At the end of the online questionnaire the respondent will be asked whether she would want to be included in a research database. This would entail that the woman’s contact details are kept securely on the protected server of the Radboud University. Women agreeing to this give permission to be contacted as potential participants for research in the future. The data on women not agreeing to be contacted as potential participants for further research are not used for this study.

From the research database, the Coordinating Investigator (CI) will contact women who have, according to the STAI-S and EPDS, at least mild symptoms of depression or anxiety. The CI informs these women about the PIP pilot trial and inquires whether they would like to receive information about the PIP pilot trial. When a woman agrees to receive information, a participant information booklet is sent to her. If a woman is not interested in receiving information, her reasons for this are recorded on a Microsoft Excel spreadsheet chart.

One week after the participant information booklet is sent, the CI will contact the woman by telephone to inquire whether she is interested in participating in the trial. This call is also an opportunity for the woman to ask any remaining questions about the pilot trial. If the woman is interested in joining the study, she will be requested to send the signed informed consent form to the Radboud University. If a woman does not want to participate in the study, the CI will inquire about her reasons for non-participation (see “Qualitative outcomes”) and will record these on a Microsoft Excel spreadsheet chart. However, according to the principles of the Declaration of Helsinki, the CI will also inform the woman that she is not obligated to reveal her reason(s) for non-participation.

After signing the informed consent form, women will be requested to fill in a screening questionnaire online for assessment of their eligibility (see “Participants” for inclusion and exclusion criteria). If women are eligible, the CI will contact them by telephone to administer the Mini International Neuropsychiatric Interview (MINI). A woman who scores as “high risk” on the MINI questionnaire or is otherwise not eligible will be informed about exclusion from the pilot trial. As stated in the informed consent form, in the case of a high risk score the woman’s general practitioner will also be informed within a maximum of 12 h about the outcome of the MINI. The remaining eligible women will be informed about inclusion and a home visit will be scheduled. They will also be randomized into one of the treatment arms.

Recruitment through centers and clinics and by using a research database was deemed appropriate for two reasons. First, it would not put undue pressure on women to consent to participate in the pilot trial. Second, it would prevent unnecessary visits by pregnant women to the Radboud University during the screening phase, as many of the women visiting the University would not fall under the eligibility criteria (i.e. the prevalence rate of elevated symptoms of anxiety and depression in pregnant women is between 10 and 20%).

A total of 2135 women need to be approached for this trial to reach a sample population of 40 participants (see Fig. 2). This number was calculated based on the following. First, from our own experience, we assume a response rate of 25% to the e-mail invitation for the online screening. Second, based on previous studies, we can expect 15% of all women who filled in the online questionnaire to screen positive for at least mild symptoms of depression or anxiety and who are thus preliminarily eligible [22, 23]. Finally, we expect that 50% of all the preliminarily eligible women interested in participating will meet all participation criteria and give informed consent. The 50% rate is based on previous studies examining the effect of dietary and psychological interventions during pregnancy [24, 25]. The expected total duration of the study from the start (enrolment of the first participants) to the last participant finishing is 13 months. No target population per site is set; recruitment will continue at all sites until the target population of 40 women is achieved. Training/information meetings will be held with organizational committee members at all involved sites prior to the start of recruitment. Each site will be monitored by Radboud University staff through regular telephone calls and e-mail correspondence, and in the case of any recruitment problems, strategies for solving them will be discussed.

**Fig. 2 Fig2:**
[figure not shown]
Consolidated Standards of Reporting Trials (CONSORT) flow diagram indicating the participant’s flow through the study. After eligibility screening, women are randomized either to the probiotic or placebo arm. Follow-up measurements take place at 34–38 weeks of pregnancy (T1), 7 days after birth (T3), and 1 month after birth (T4). EPDS, Edinburgh Postnatal Depression Scale; LEIDS-R, Leiden Index of Depression Sensitivity-Revised; PRAQ-R, Pregnancy Related Anxiety Questionnaire-Revised

#### Start of the intervention

Prior to the first home visit, the participant fills in the baseline questionnaire (see Fig. 1). During the first home visit, the participants receive the probiotic/placebo product and kits from the CI who is blinded to the intervention. The participant collects the first stool and vaginal samples at home prior to the start of taking the probiotic/placebo product. These samples are kept in the participant’s freezer and handed over to the CI or research assistant at time point 1 (t1) or t4. After stool and vaginal fluid collection, the participant starts with the probiotic/placebo product intake once per day until time of delivery.

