#### Maternal vaginal microbiota

Two vaginal samples will be collected to study changes in vaginal microbiota between baseline and 8 weeks after the start of the intervention. Participants will collect the samples by rotating swabs 3–4 cm deep into the vagina. Samples will be collected by the validated self-collection method using dry swabs [65]. The samples will be immediately stored at − 20 °C, collected by investigators at t1 or t4 and then stored at − 80 °C at the Radboud University. Microbial composition will be determined using polymerase chain reaction (PCR) sequencing methods at affiliated universities experienced in this type of analysis; the location for these analyses has yet to be determined.

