#### Infant intestinal microbiota

Parents will collect two infant fecal samples at home on weeks 1 and 4 using similar collection methods to those applied in our previous studies [36, 38], to measure the relative abundance of infant intestinal bacteria. Samples will be immediately stored by the participants at − 20 °C, collected by investigators at t3 and taken back to the University for storage at − 80 °C. The microbial composition of the stool samples will be analyzed using PCR sequencing methods.

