### Adherence assessment

To facilitate adherence to the study protocol and increase the validity of data, throughout the study the CI will inquire about participants’ experiences during the trial, including potential problems with the probiotic/placebo product intake, questionnaires and collection of vaginal and stool samples. In the case of problems, the CI will discuss solutions with the participants to improve adherence. After 8 weeks of probiotic intake (t1) the CI will call to inform the participant about the number of sachets consumed during the intervention period and will record the number on the CRF. At t4, the CI will measure compliance during a home visit by counting the sachets that are left from the previous weeks and notes the data on the CRF. Electronic questionnaire data collected from participants will be downloaded into a designated secure Radboud University study computer to check for missing data. In the case of missing questionnaire data, the CI will send an e-mail reminder to the participant with the request to fill in the questionnaire as soon as possible. The CI will record non-adherence and non-retention (i.e. consent withdrawn and loss to follow up) on the CRFs, and the reasons for non-adherence and non-retention if the participants are willing to reveal these.

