### Strategies to improve adherence to the intervention protocol

During the first home visit when the participants receive the probiotic/placebo product and sampling kits, the CI will provide face-to-face adherence reminder sessions. Similar adherence reminder sessions will be held by phone at t1 and t3, and face-to-face at t4. This will include:Explanation about the importance of adhering to study guidelines on the daily intake of the study product, electronic questionnaires and collection of vaginal and microbial sampling.Instructions about taking the probiotic/placebo product, including timing, preparation, storage, and what to do in the event of missing a dose.Reinforcement that the sachets contain either probiotics or placebo.Instructions about the purpose and use of vaginal swabs and microbial collection tubes, and temporary storage of vaginal and microbial specimens after collection. Instructions on paper will be provided at t0 (see Additional file 3D-E).Notification of the importance of contacting the CI if experiencing any problems related to intake of the probiotic/placebo product (e.g. symptoms, lost sachets), electronic questionnaires or the collection of vaginal and/or microbial samples.Reinforcement that, if there are any questions related to the study or problems occur during the intervention period, the CI (or in case of absence, another research member) can be contacted by phone or e-mail.

Within 2 days after the first home visit, the CI will contact the participant to ask whether there were any problems with the probiotic/placebo product or questionnaires, and to inform them about the time/date of collecting vaginal and stool samples. In case there are problems, simple strategies for enhancing adherence to study protocol will be discussed. The participant will also have the opportunity to ask the CI any remaining questions.

Participants will receive an electronic reminder at t1 to fill in questionnaires and to collect vaginal and microbial samples, again including the instructions about the use of vaginal swabs and microbial tubes and storage of specimens after collection. The CI will contact the participant 2 days after the first reminder, to request the time/date of collection of microbial and vaginal samples. In the case of problems, the CI will discuss with the participant simple strategies to enhance collection and/or filling in of questionnaires.

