#### Secondary outcomes

Although the aim of this pilot trial is to assess the feasibility and acceptability of running a definitive trial, the secondary psychological, behavioral and biological outcomes will be analyzed to mimic the definitive trial. All analyses of the secondary outcomes will hence be viewed as preliminary and thus interpreted with caution.

Outcomes will be analyzed per-protocol and by intention to treat (ITT). For the per-protocol analysis, participants who are found ineligible after randomization or deviated from the probiotics/placebo product intake (i.e. less than 80% intake) will be excluded from the main analysis. For the ITT analysis, all randomized participants, regardless of protocol adherence or dropouts (i.e. participants who withdraw consent for continued follow up), will be included in the main analysis. Participants will be analyzed according to the group to which they were originally allocated. In case of missing data, missing values will be imputed. Student’s *t* test will be used to analyze normally distributed data and the nonparametric Mann–Whitney U test will be used to analyze non-normally distributed data. For comparisons of more than two groups (e.g. differences in the relative abundance of bacteria at the level of phylum up to the level of order in microbial samples), analysis of variance with Tukey’s post-hoc test of the intervention and placebo group at the primary endpoint will be compared using a one-way analysis of covariance (ANCOVA) model, where the covariate will be the baseline score. In addition, the effect size will be computed to estimate the required sample size for the future large-scale trial. The significance level for statistical analysis is set at *p* < 0.05.

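### Infant stool from weeks 1 and 4 is to be picked up at t3 (day 7 after birth), before the week-4 sample exists, and Table 1 places the infant-sample criterion at two time points in pregnancy

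*Protocol article*

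**What the plan says.** Under Infant intestinal microbiota, the protocol article states: "Parents will collect two infant fecal samples at home on weeks 1 and 4". Families freeze the samples at home, and the same sentence then has them "collected by investigators at t3 and taken back to the University for storage at − 80 °C".

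The legends of Figures 1 and 2 define t3 as day 7 after birth and t4 as one month after birth. Under Strategies to improve adherence, the contacts are described as follows: "Similar adherence reminder sessions will be held by phone at t1 and t3, and face-to-face at t4". Under Adherence assessment, t4 includes a visit to the home: "At t4, the CI will measure compliance during a home visit by counting the sachets that are left from the previous weeks". Hair is also cut by the coordinating investigator at 4 weeks postpartum (Maternal hair cortisol).

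Two tables depend on the infant samples:

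- Table 2 defines infant faecal microbiota as a change between t3 and t4.
- Table 1, compliance item 8, asks what proportion of participants collect all infant samples at t0 and t1, with a progression criterion of 90%.

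For the mothers' samples, hand-over is placed at contacts after the baseline collection. Start of the intervention says "These samples are kept in the participant’s freezer and handed over to the CI or research assistant at time point 1 (t1) or t4", and the section on vaginal microbiota says they are "collected by investigators at t1 or t4 and then stored at − 80 °C at the Radboud University".

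**The concern.** The article gives three timings for the infant samples, and they do not fit together. Collection is in weeks 1 and 4, pick-up is on day 7, and the progression criterion sits at two time points before the infant is born.

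The infant microbiota outcome needs two samples per infant. If the pick-up rule is followed as written, the second is never covered by it, and the change cannot be computed. The imputation announced under Statistical analysis could not repair that, since there would be no observed week-4 values to impute from.

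The feasibility side is affected too. The article says the secondary outcomes are there partly to establish that such data can be collected for a later full trial. A criterion tied to t0 and t1 cannot be evaluated for infant stool at all.

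**Working it through.** The plan gives no figure on this point to reproduce. The check compares the schedule with the collection and retrieval rules.

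**1. Time points (legends of Figures 1 and 2).** t0 is 26–30 weeks of pregnancy, t1 is 34–38 weeks of pregnancy, t3 is day 7 after birth, and t4 is one month after birth.

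**2. Does each infant sample exist at t3?** The week-1 sample can exist by day 7. The article gives no day for the week-4 sample; I take it to fall between day 21 and day 28.

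- Earliest gap after t3: 21 − 7 = 14 days.
- Latest gap after t3: 28 − 7 = 21 days.

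On either bound, the week-4 sample does not exist at the stated pick-up.

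**3. Is there a visit at t3?** The adherence session at t3 is by phone. The article describes no t3 visit, so even the week-1 pick-up has no matching contact in the text. The article does not rule such a visit out.

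**4. Is there a visit at t4?** Yes. The face-to-face session, the sachet count at home and the hair sample all fall there, and t4 coincides with or follows the week-4 sample.

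**5. What does the analysis need?** The Table 2 metric is the t4 value minus the t3 value, so one sample alone gives no outcome.

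**6. Can Table 1 item 8 be evaluated?** t0 and t1 are both scheduled in pregnancy, so no infant stool exists at either. Item 7, for the mothers' samples, uses the same t0 and t1, and there they fit. Item 8 may have inherited them, but that is a guess.

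**7. What would a t4 pick-up add to home storage?** The week-1 sample would wait about 28 − 7 = 21 days longer. For comparison, the mothers' baseline samples already wait until t1 at the earliest: 34 − 26 = 8 weeks, or 38 − 30 = 8 weeks. The added three weeks is shorter than the home storage the plan already accepts for them.

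**8. How many are affected?** The rule applies to every infant. Multiple pregnancy is an exclusion, so 40 women means 40 infants. The rule is the same in both arms, so it gives no reason to expect a difference between arms.

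**The case against.** The strongest reply is that this is a slip in a label. A t4 home visit exists and the investigator comes to take hair at 4 weeks, so the week-4 stool can be picked up then whatever the sentence says. The outcome is exploratory, and the article says such results will be interpreted with caution. Item 8 carries no asterisk, so it is not a key progression criterion.

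Most of this stands. Nothing shows that any week-4 sample would be lost in practice. It does not remove the point, however. The article does not leave the pick-up time to a fuller document; it states one, and the one stated cannot work. The same holds for item 8.

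A reader might go further. Mothers' samples and leftover sachets stay at home, and the intention-to-treat analysis takes in all randomized women "regardless of protocol adherence or dropouts (i.e. participants who withdraw consent for continued follow up), will be included in the main analysis". One could infer that women who withdraw lose everything they had already given, and that it is then imputed. The documents do not support this:

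- t1 is a named hand-over point, so a woman who leaves after t1 may already have handed over her samples. The phone contacts at t1 are reminder and sachet calls, and nothing says that no pick-up takes place then.
- The maternal metric is the change from baseline to t1. A woman who leaves before t1 has no t1 value, so recovering her baseline sample would not complete the change.
- Sachet use is recorded at the t1 call, and the key intake criterion covers t0 to t1. The t4 count is not its only source.
- Compliance is a descriptive primary outcome. The imputation text stands under the secondary outcomes, and nothing says sachet counts are imputed.
- What happens to stored material at withdrawal is operational detail that a condensed article may leave to the full protocol.

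**Conclusion.** The point holds for infant stool only. The stated pick-up at t3 precedes the week-4 sample by 14 to 21 days, taking week 4 as days 21 to 28. Table 2 requires that sample for every infant, and Table 1 item 8 sets its criterion at times when no infant sample can exist.

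Taken literally, the rule leaves the week-4 sample of all 40 infants outside the stated pick-up. Taken with the t4 home visit, it is most likely a wrong or incomplete time point, and actual loss is unlikely. No conclusion about maternal samples, sachet counts or withdrawn women follows from it.

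This is a minor correction to an exploratory outcome and to one non-key progression criterion. It is worth making because the pilot is meant to test these procedures for a full trial.

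**What to change.** - **Infant intestinal microbiota:** change the pick-up from t3 to t4, so that both infant samples are retrieved at the existing t4 home visit.
- **Table 1, compliance item 8:** change the time points from t0 and t1 to t3 and t4, in line with Table 2.

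The cost is two wording changes and no extra visit. The downside is that the week-1 sample stays about three weeks longer in the home freezer before transfer to the university's colder storage. At submission, 35 women had signed consent and 18 had completed the study, so the change can serve only the remaining participants and the full trial. For those who have completed, the report should state when their infant samples were actually picked up.
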